### Statistical Considerations

The primary analysis set comprises all enrolled patients who received at least one vaccination within the COVID-19 vaccination standard [20]. The statistical analysis is essentially descriptive and focuses on estimation of the time to event, that is, primary and secondary end points. The event-time distributions are described by the Kaplan-Meier method [24] with pointwise 95% confidence bounds [25] (18, “log-log”). Relevant percentiles (eg, quartiles) with 95% CIs are derived. Generally, quantitative variables are summarized by mean, SD, and percentiles (0, 25, 50, 75, 100), and qualitative variables by absolute (ie, count) and relative (ie, percentage) frequencies. Extreme values (“outliers”) are flagged and listed.

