## Introduction

The novel SARS-CoV-2 was identified in December 2019 as a cause of severe pneumonia, acute respiratory distress syndrome, and potential multiorgan failure in humans [1,2]. The disease known as COVID-19 has turned into a worldwide pandemic, causing substantial morbidity and mortality, and is now (2024) considered an endemic disease. As of December 15, 2024, the World Health Organization reports a total of 7,079,587 COVID-19 deaths worldwide [3]. Patients who are immunocompromised, such as those with hematological malignancies, are highly affected by SARS-CoV-2 infections due to the high risk of severe courses of infection [4-8]. COVID-19 may not only result in a delay or discontinuation of the treatment for the underlying diseases but also result in high mortality rates of above 30% [4-6,9,10]. Prevention strategies are therefore focused on avoiding SARS-CoV-2 infection in these vulnerable patients and reducing the risk of critical disease following infection. This is addressed by nonpharmacological and pharmacological interventions. Nonpharmacological interventions such as wearing masks, physical distancing, and respiratory hygiene are effective for reducing SARS-CoV-2 transmission but were withdrawn for the general population by state authorities as of June 2022. For example, masking in public is no longer mandatory in many countries. Pharmacological interventions included several antiviral drugs as well as various therapeutic monoclonal antibodies that lost neutralizing capacity with the emergence of Omicron variants [11,12]. At the end of 2020 and the beginning of 2021, the first messenger RNA vaccines against COVID-19 were proven to be effective in the prevention of severe SARS-CoV-2 infection and licensed for use [13-15]. The German Standing Committee on Vaccination of the Robert Koch Institute (RKI) has been recommending 3 antigen contacts (infection or vaccination) to complete basic immunization, of which at least one should be by vaccination. Annual booster recommendations are advised for groups at high risk, such as people with an impaired immune response [16]. COVID-19 vaccination, therefore, represents the mainstay of COVID-19 prevention. Efficacy and safety have been demonstrated for several vaccines, leading to currently 15 vaccines listed by the Paul Ehrlich Institute in Germany and with marketing authorization in Europe (as of October 2024) [17]. Studies have shown that COVID-19 vaccination is efficient in patients who are immunocompromised. However, lower levels of antibodies have been reported in this patient group [18,19]. Patients who are immunocompromised had been excluded from the majority of registered studies. Further, studies focused mainly on B-cell immune responses, resulting in uncertainty regarding the extent of immune response and the role of T cell–generated immune response in these patients. The aim of this study is to determine the immunogenicity and reactogenicity of an implemented standard-of-care (SOC) COVID-19 vaccination strategy (Multimedia Appendix 1) in patients who are immunocompromised [20].

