**Primary end point**
Time to reach an adequate immune response according to the recent version of the COVID-19 vaccination standard-of-care [20] after repeated messenger RNA (mRNA) vaccinations (Multimedia Appendices 1 and 3)

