**Premature withdrawal from the study**
In case a patient fulfills one of the following criteria, the patient must be withdrawn from the studyPatient has reached an adequate immune response as defined in the recent version of the COVID-19 vaccination standard [20] at the first visitIn case a patient has to withdraw prematurely from the study, all data that have been collected between enrollment and withdrawal will be used for the analysis.

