### Sample Size

The target sample size of 100 is sufficient to estimate event-free probabilities around the median “survival” with acceptable precision (half-width of a 95% CI) of about 10% for censoring rates less than 20% (Table 3).

**Table 3 table3:** Sample size calculation.

Number of events	Half width^a^ (%)
100	9.7
90	9.9
80	10.2
70	10.6
60	11.1
50	11.8
40	13.3
30	15.4
20	19.7
10	21.7
0	—^b^

^a^“Absolute” percentage points.

^b^Not applicable.

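### Under plain Kaplan-Meier, death before response or before waning can enter only as censoring, which overstates the share of patients who reach each event

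*Protocol article*

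**What the plan says.** The primary end point is "Time to reach an adequate immune response according to the recent version of the COVID-19 vaccination standard-of-care". The time-to-event secondary end points are the times at which a titer rises to a threshold or, in patients already vaccinated successfully, falls below it. None of the visible definitions mentions death.

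Statistical Considerations says that the analysis "focuses on estimation of the time to event, that is, primary and secondary end points". It names one estimator, "The event-time distributions are described by the Kaplan-Meier method", "with pointwise 95% confidence bounds" of the log-log type, with quartiles derived from the curve. The analysis set is inclusive: "The primary analysis set comprises all enrolled patients who received at least one vaccination within the COVID-19 vaccination standard". The textbox on premature withdrawal adds that "all data that have been collected between enrollment and withdrawal will be used for the analysis".

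The Sample Size section rests on the same estimator: "The target sample size of 100 is sufficient to estimate event-free probabilities around the median" survival time, with a half-width of about 10 points for censoring below 20%. That censoring rate is not divided by cause.

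**The concern.** Kaplan-Meier handles a censored patient as one who could still have the event later, at the same rate as those still under observation. A patient who has died cannot. When deaths are censored, one minus Kaplan-Meier describes a hypothetical cohort in which nobody dies. It does not estimate the proportion of vaccinated patients who reach an adequate response.

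Death before response is foreseeable here. Eligibility is stage 3 immunosuppression, which includes hemato-oncological disease, and the visit schedule has its own footnote for patients after stem cell transplantation or CAR-T cell treatment. The results are meant to inform vaccination and booster schedules, so response shares and upper percentiles will be read as what happens to real patients. The waning curves have the same difficulty: a responder who dies with a titer still above the threshold is counted as someone who would wane later.

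**Working it through.** **Inputs from the document.** N = 100; pointwise 95% log-log limits; half-width about 10 points with censoring below 20% (Table 3); visits at 28-day intervals (Table 1).

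**Inputs assumed, because the document gives no death or dropout rate.** A share d of 5% to 20% dying before response, where the upper end corresponds to all of the plan's 20% censoring ceiling being death; constant hazards; and the per-visit probabilities in step 4.

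**1. Reproduce Table 3.** At S = 0.5 without censoring, SE = √(0.25/100) = 0.05 and k = exp[1.96 × 0.05 / (0.5 × ln 2)] = 1.327. The half-width is (0.5^(1/k) − 0.5^k)/2 = (0.593 − 0.399)/2 = 9.7 points, as printed. Simulation with independent exponential censoring (1000 samples per row) gives 9.9 and 10.2 points for 90 and 80 events, also as printed. The rows that support N = 100 are therefore consistent with ordinary independent censoring. Rows with 30 or fewer events depend on the censoring pattern and were not matched; they do not matter here.

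**2. Formula.** Set the response hazard to 1 and the death hazard to d/(1 − d), so that a share d dies before responding. If F is the value of one minus Kaplan-Meier with deaths censored, the true cumulative incidence is

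CIF = (1 − d) × [1 − (1 − F)^(1/(1 − d))].

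Example, d = 0.20 and F = 0.50: 0.8 × (1 − 0.5^1.25) = 0.8 × 0.5796 = 46.4%.

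| d | CIF when 1−KM is 50% | gap | CIF when 1−KM is 75% | gap | CIF at plateau (1−KM tends to 100%) | gap |
|---|---|---|---|---|---|---|
| 5% | 49.2% | 0.8 | 72.9% | 2.1 | 95% | 5 |
| 10% | 48.3% | 1.7 | 70.7% | 4.3 | 90% | 10 |
| 20% | 46.4% | 3.6 | 65.9% | 9.1 | 80% | 20 |

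The same formula serves the waning end points, with d the share of responders who die before their titer falls.

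**3. Percentiles.** The time at which the CIF reaches q is −(1 − d) × ln[1 − q/(1 − d)], against −ln(1 − q) for Kaplan-Meier.
- Median: later by a factor of 1.02, 1.05 and 1.13 for d = 5%, 10% and 20%.
- Time to 75%: 1.480, 1.613 and 2.218 against ln 4 = 1.386, that is later by a factor of 1.07, 1.16 and 1.60.

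**4. Check in 28-day intervals.** Let each interval carry death probability q, then response probability p = 0.30 among survivors not yet responding. After six intervals 1−KM = 1 − 0.7^6 = 88.2%, and CIF = p(1 − q) × [1 − ((1 − p)(1 − q))^6] / [1 − (1 − p)(1 − q)].

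| q per interval | CIF after 6 intervals | gap | died before response |
|---|---|---|---|
| 0.5% | 87.1% | 1.1 | 1.5% |
| 1% | 86.0% | 2.2 | 2.9% |
| 2% | 83.9% | 4.4 | 5.7% |
| 5% | 77.7% | 10.5 | 13.6% |

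The median moves by at most one visit. At q = 2% the second-visit values are 51.0% (1−KM) and 0.294 × (1 + 0.686) = 49.6% (CIF), which straddle 50%. With 25% or 15% response per visit and 2% to 6% competing exit after it, the median is the same visit under both methods (the third and the fifth).

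**5. Leaving alive is different.** Suppose 20% leave alive and 1−KM reads 50%. The true share is 46.4% if leavers never respond, 48.4% if their response hazard is half that of stayers, 50% if it is equal, and 51.3% if it is 1.5 times as high.

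**The case against.** The strongest objection is that no sentence says deaths are censored. The article condenses a longer protocol, Multimedia Appendix 3 defines the primary end point and is not shown, and censoring rules are often left to the SAP. This stands as a caution: the censoring is inferred. It does not remove the point, because the article names the estimator and sizes the study on it. With end points defined as in the visible text, plain Kaplan-Meier has no other place for a death.

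A second objection is that the analysis is descriptive, never equates one minus the curve with the share responding, and may target waning among the living. That is a fair reason to keep the Kaplan-Meier curve, but as a supplement, since readers will take the curve as the share of patients.

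Several stronger readings are tempting, and the document does not support them:
- That everyone who leaves inflates the curve. Leaving alive biases it only if leavers differ from stayers, and in either direction. The one withdrawal criterion listed concerns patients with an adequate response already at the first visit; censoring them instead of counting events would bias the curve downward. Nothing says that relapse or new therapy ends participation.
- That slow responders are censored selectively because they are followed longer. Kaplan-Meier conditions on those still at risk, so longer exposure alone is no bias.
- That exits before waning inflate the response share. Those patients have already responded.
- That the mortality above 30% in the Introduction is this cohort's death rate. It concerns patients with COVID-19.

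**Conclusion.** The point holds for death. If any patient dies before responding and is censored, one minus Kaplan-Meier exceeds the share who reach an adequate response; censoring death before waning likewise overstates the share who wane. The direction is certain given such deaths. The size is not, because the document gives no death rate.

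Under constant hazards and an assumed 5% to 20% dying before response, the effect near the median is small beside the plan's half-width of about 10 points. It comes close to that half-width at the upper quartile in the worst case and equals the whole death share at the plateau. Unlike sampling error, it does not shrink with more patients. A reader might infer that the reported median would be materially too short; the calculations show only a modest shift. The conclusion also assumes that the documents not shown do not already provide for death.

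**What to change.** In Statistical Considerations, report the response and waning end points as cumulative incidence (Aalen-Johansen) with death before the event as a competing event. Derive the quartiles and their intervals from that curve, noting that a quartile is not reached if the curve levels off below it. Keep Kaplan-Meier as a supplementary analysis, labelled as describing the event rate among patients still alive and under observation.

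State that patients who leave alive are censored at their last titer. Add a sensitivity analysis for informative dropout by reason for exit.

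Record the date and reason of every exit, including death, if the eCRF does not already do so. The visible safety rules collect serious adverse events only for 7 days after each vaccination, and serious adverse drug reactions throughout, so a later death unrelated to the vaccine might not be captured by them.

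The cost is a change of wording, standard software, possibly one eCRF item, and slightly lower reported response rates. N = 100 need not change. Recruitment was still open, with 32 patients enrolled in August 2024.

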### Sample Size

The target sample size of 100 is sufficient to estimate event-free probabilities around the median “survival” with acceptable precision (half-width of a 95% CI) of about 10% for censoring rates less than 20% (Table 3).

**Table 3 table3:** Sample size calculation.

Number of events	Half width^a^ (%)
100	9.7
90	9.9
80	10.2
70	10.6
60	11.1
50	11.8
40	13.3
30	15.4
20	19.7
10	21.7
0	—^b^

^a^“Absolute” percentage points.

^b^Not applicable.

### Ethical Considerations

#### Ethics

This study will be conducted in accordance with the protocol and with the following:

Consensus on ethical principles derived from international guidelines, including the Declaration of Helsinki and the Council for International Organizations of Medical Sciences international ethical guidelinesApplicable ICH-GCP guidelines dated July 1996 and its Addendum E6(R2) of June 2017

The study was approved by the lead Ethics Committee of the University of Cologne (Cologne, Germany; 22-1279-NIS), and approval by the responsible Ethics Committee for the study sites Aachen and Essen followed.

#### Obtaining Informed Consent

Patients will be informed verbally and in writing in a comprehensible language about the nature, scope, and possible consequences by the PI or subinvestigator. This includes consent to data access by representatives of the lead PI of the Investigator Initiated Trial (eg, monitors). The patient will be informed of potential benefits and possible risks associated with participation in the study. Of note, risks associated with study participation are considered minimal and are limited to data protection. No additional interventions (eg, vein puncture) or treatments are foreseen as part of study participation. Patients will be informed that withdrawal of consent is possible at any time without giving a reason and without jeopardizing the patients’ further course of treatment. It is the PIs or subinvestigators responsibility to ensure that the patient fully understands the implications of participation in the study. Patients must not be enrolled in the study unless they have consented to take part in writing. The patients’ medical records must contain a statement that written informed consent was obtained, including the date on which the consent was obtained. In addition, the authorized person at the study site (investigator or subinvestigator) who obtains the informed consent must also sign the informed consent form (ICF) according to the ICH-GCP guidelines. Patients must be reconsented to the most current version of the ICFs during their participation in the study if relevant. The signed consent form is archived at the study site as the original. Patients receive copies of the signed ICF. The ICF and all other documents handed out to the study participants will be submitted to the ethics committee before use. Monitors will check that the most recent ICF was used before the patient’s inclusion and that it was dated and signed by the patient himself or herself.

## Results

As of August 2024, the Auto-COVID-VACC study has enrolled 32 patients. The study is still in the recruitment phase.

## Discussion

### Overview

The COVID-19 vaccination standard, implemented at the University Hospital of Aachen, Cologne, and Essen, poses an individual vaccination approach for each patient depending on their individual immune response. The evaluation of the data on humoral and cellular immune responses generated within this COVID-19 vaccination standard will be used to optimize vaccination schedules for patients who are immunocompromised. Results may further help to identify the optimal timing of booster vaccinations within this patient population and their subsets and will lead to increased rates of protection against severe SARS-CoV-2 infections. As the patients included in this study have varying underlying diseases (eg, multiple myeloma, Hodgkin lymphoma) and follow different treatment concepts (eg, chemotherapy, immunotherapy, hematopoietic stem cell transplantation), study results may identify risk and treatment factors on the humoral and cellular immune response in patients receiving COVID-19 vaccination.

### Limitations

This study design has several a priori limitations. The study focuses on COVID-19 vaccination only. Patients with SARS-CoV-2 infection are excluded when tested positive; however, studies have shown that SARS-CoV-2 infections also induce immune responses and therefore increase protection [26]. Future study results have to be interpreted cautiously due to the potential risk of bias as data are collected as part of an observational study and in the frame of a SOC COVID-19 vaccination schedule. Patients therefore are not randomized. Further, potential confounders are not included in the statistical analysis.

### Conclusions

Patients who are immunocompromised are at high risk for severe SARS-CoV-2 infections. Data on the efficacy of COVID-19 vaccination in this group are still lacking. The study aims to determine the immunogenicity and reactogenicity of the COVID-19 vaccination standard in patients who are immunocompromised by evaluating the available data on humoral and cellular immune responses.

## Appendix

Multimedia Appendix 1 COVID-19 vaccination standard.

Multimedia Appendix 2 Stages of immunosuppression (Table S1); Definition and grading of solicited adverse events (Table S2).

Multimedia Appendix 3 Primary end point definition for the Auto-COVID-VACC trial.

## Abbreviations

ADR: adverse drug reaction
AE: adverse event
CAR: chimeric antigen receptor
CTCAE: Common Terminology Criteria for Adverse Events
CTCC: Clinical Trials Centre Cologne
eCRF: electronic case report form
ICF: informed consent form
ICH-GCP: Good Clinical Practice (of the International Council for Harmonisation of Technical Requirements for Pharmaceuticals for Human Use)
IgG: immunoglobulin G
PI: principal investigator
SOC: standard of care
